### 2.12. Statistical Analysis

#### 2.12.1. Overview

We will validate the predictive performance of CHA_2_DS_2_-VASc for 90-day recurrence and secondary outcomes in the AF patient cohort by examining discrimination (AUC), calibration (calibration curves and Brier scores), and clinical utility (decision curve analysis). For CPR updating, we will use logistic regression (LR), extreme gradient boosting (XGBoost), and multilayer perceptron (MLP) models, with training and tuning performed through 5 × 2 nested cross-validation. The MLP model will employ transfer learning to incorporate information from the non-AF cohort. Model performance will be assessed on a hold-out test set using AUC, calibration curves, F1 score, and accuracy. We will utilise Shapley additive explanations (SHAP) for model interpretation and to construct two CPRs per model: one based on SHAP main effects and another incorporating both SHAP main and interaction effects. These CPRs will be evaluated against each other, CHA_2_DS_2_-VASc, and default strategies, with test tradeoff analysis to balance ease-of-use with clinical utility.

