#### 2.12.5. Updating

##### Models

LR, XGBoost, and MLP classifier models will be used to establish the updated CPR. LR and XGBoost will power our primary analyses, and MLP our secondary analyses.

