Each of the CPRs will subsequently be augmented by integrating interaction effects. This purports to better accommodate for the fact that a given feature may be more impactful in the presence of one of its counterparts. Mean (and not mean *absolute*) SHAP interaction values will be used in order to distinguish between synergistic and redundant interactions. The decile rank of each of the twenty-eight mean SHAP interaction values from each model will be calculated. A dot plot will be provided to visualise each feature-pair’s mean SHAP interaction value relative to other pairs. (We speak of twenty-eight mean SHAP interaction values because there are eight features, and (*i*, *j*)- and (*j*, *i*)-values capture the same interaction effect, while (*k*, *k*)-values capture main effects and were the object of the above paragraph). Dealing with a large number of feature-pairs, we will use stringent percentiles in selecting interaction effects for inclusion. The 90th percentile of the sample of twenty-eight mean SHAP interaction values will be computed. Feature-pairs with mean SHAP values above this threshold will be selected as the most important synergisms. Feature-pair selection will also incorporate domain knowledge, as some feature-pairs have well-established synergisms that may merit inclusion even if they fall somewhat short of the 90th percentile cutoff. Examples include CHF and age [121], hypertension and age [122], and hypertension and DM [123]. Selected feature-pairs will be integrated into the CPRs as accompanying rules: ‘if both feature *i* and *j* of the pair are present in the patient, add one additional point to the patient’s total score’. To mitigate overfitting, we will cap the number of points that can be added to accommodate synergisms to three. We will further cap the number of interaction pairs retained at a maximum of three. The augmented CPRs will be summarised in tabular form and their acronyms labelled with an asterisk (e.g., CHA_2_DS_2_-VASc*). A worked example of the CPR development process here described can be found in Appendix S6 in Supplementary Materials file S3.

Both non-augmented and augmented CPRs will undergo evaluation. See “CPR Evaluation”.

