NB will be plotted on the *y*-axis against risk threshold on the *x*-axis to yield a decision curve for each CPR. These curves, including the one for CHA_2_DS_2_-VASc, will be presented in a single figure to facilitate comparison. Additionally, we will plot lines representing the default strategies of ‘treat all’ and ‘treat none’, corresponding to scenarios where all or no patients are assumed to suffer 90-day recurrence, respectively. Incidentally, these lines will intersect at the observed prevalence of 90-day recurrence in our test set. A CPR will be considered clinically useful at a given risk threshold only if its NB exceeds that of both default strategies. Conversely, if a CPR’s NB is lower than either default strategy, it will be deemed clinically harmful. Our initial analysis will focus on determining whether the CPRs have higher NBs than the default strategies across the selected risk thresholds. We will then proceed to comparing the CPRs, ranking them based on descending NB, and identifying the three CPRs with the highest clinical utility (Table 3 and Table 4).

If an augmented CPR ranks among the three highest, we will perform test tradeoff analysis to compare it with the closest-ranking non-augmented CPR. The test tradeoff, calculated as Δ*NB*, represents the minimum number of additional tests per true positive required to justify the augmented CPR’s use, considering its added cost [124]. Of course, in our case, cost is not financial, but the additional time and reduced convenience associated with augmented CPRs, which include accompanying rules and are thereby more unwieldy than their non-augmented counterparts. If the NB differences across thresholds are small, the test tradeoff will be large, suggesting that the simpler CPR may be better, all things considered. After all, CHA_2_DS_2_-VASc owes its widespread adoption to its parsimonious, back-of-the-envelope nature. For clarity, we will report test tradeoffs in terms of both true positives and true negatives. The same approach will be applied to CPRs developed using MLP, where the test tradeoff will help decide whether the increased NB justifies the involvement of a less interpretable model. Ultimately, the purpose of reporting test tradeoffs will be to highlight which CPRs—if any—would be conveniently deployable without sacrificing significant clinical utility, and *not* to dismiss higher cost CPRs from future consideration.

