Primary: Does the acute context of AFAIS, and the importance of the index event, call for a CPR bespoke to early secondary prevention? In other words, are the main effects of the constituent features of CHA_2_DS_2_-VASc different post-stroke? Besides main effects, are there synergistic or other non-linear interaction effects between stroke history and the constituent features of CHA_2_DS_2_-VASc that can further improve prediction of 90-day AFAIS recurrence? Secondary: How do CPRs trained to capture 90-day AFAIS recurrence perform with regard to secondary outcomes (7-day recurrence, 7- and 90-day HT, 90-day decline in functional status, and 90-day all-cause mortality)? Exploratory: How do CPRs trained to capture 90-day AFAIS recurrence perform with regard to recurrence among non-AF AIS patients?	Primary: LR and XGBoost can capture the main effects of the constituent features of CHA_2_DS_2_-VASc in the context of secondary prevention. XGBoost is also equipped to capture complex functional relationships between the features. The outputs of these models can be employed to construct CPRs that outperform CHA_2_DS_2_-VASc for predicting 90-day recurrence in AFAIS patients. Specifically, fair (AUC < 0.8) to good (< 0.9) discrimination can be achieved for this high-risk group, alongside improved calibration and clinical utility relative to CHA_2_DS_2_-VASc. Secondary: The resulting CPRs also outperform CHA_2_DS_2_-VASc for predicting secondary outcomes.	LR and XGBoost models: Discrimination assessed using AUC and calibration curves. Calibration assessed using calibration curves, slopes, and Brier scores. Additional metrics: F1 score, accuracy, precision, sensitivity, specificity, Youden index, PPV, NPR, PLR, NLR. Resulting CPRs: Discrimination assessed using AUC and calibration curves. Calibration assessed using calibration curves, slopes, and Brier scores. Clinical utility assessed via DCA relative to default strategies as well as CHA_2_DS_2_-VASc. Test tradeoff analysis will be used to balance ease-of-use with clinical utility.	Primary: LR—680 patients deemed necessary, see Appendix S5.3 in Supplementary Materials file S3. XGBoost—learning curve analysis and KL divergence will afford post hoc insight on suitability of sample size. 75% of AF dataset will be used, comprising 2072 AFAIS patients. Remaining 25% (691 patients) will be withheld as test set. Secondary: Entire AF dataset will be used, comprising 2763 AFAIS patients. Exploratory: Entire non-AF dataset will be used as supplementary test set, comprising 7809 AIS patients.	Models will be instantiated (LR with L2 regularisation and XGBoost with default hyperparameters) on AF dataset, randomly split into training (***T***, 75%) and test sets (***t***, 25%), preserving distribution of outcomes. Nested cross-validation (5 × 2) will be employed for training and hyperparameter tuning. After hyperparameters are optimised, final models will be retrained using the entire training set. The test set ***t*** will then be used for evaluation of final LR and XGBoost models, focusing on discrimination and calibration. Feature importance will be reported via coefficients and odds ratios (ORs) for LR and feature gain for XGBoost. To derive CPRs from these models, SHAP will quantify both main effects and interaction effects of predictor variables. Main effects, represented by mean SHAP values, will be used to rank and assign scores to each predictor, enabling the creation of interpretable and clinically applicable CPRs. Interaction effects, captured through SHAP interaction values, will further refine our CPRs by identifying significant synergistic or redundant relationships between predictors. These interactions will be incorporated into so-called ‘augmented CPRs’ in the form of accompanying rules. Both non-augmented and augmented CPRs will be evaluated on the test set ***t*** in terms of discrimination, calibration, and clinical utility. Clinical utility will be measured using NB via DCA, plotting NB against risk thresholds within the 0.01–0.20 range. The CPRs will be compared on the basis of clinical utility to one another, CHA_2_DS_2_-VASc, and default strategies (‘treat all’ and ‘treat none’). Test tradeoff analysis will evaluate whether any incremental benefit in clinical utility observed with augmented CPRs justifies the added complexity of incorporating accompanying rules. Secondary: CPRs (and not models) will be evaluated on the entire AF dataset for each secondary outcome via discrimination, calibration, and clinical utility. Exploratory: CPRs (and not models) will be evaluated on the entire non-AF cohort to assess generalisability and compare their clinical utility when applied to an unseen yet closely related patient population.	Discrimination will be classified as follows [101]: AUC of 0.81–0.90 = good, 0.71–0.80 = fair, 0.61–0.70 = modest, and 0.51–0.60 = poor. Miscalibration is detrimental to medical decision making and poor calibration has been coined the Achilles heel for CPR applicability [102]. As such, we consider at least as important as discrimination and give precedence to clinical utility, which provides a more comprehensive evaluation by integrating both discrimination and calibration when interpreting the performance of our CPRs. CPRs will be considered clinically useful at a given risk threshold only if their NBs exceed those of both default strategies. Of those deemed useful, we will rank the CPRs (including CHA_2_DS_2_-VASc) based on NB across the 0.01–0.20 risk thresholds. Test tradeoff (∆*N**B*) will be interpreted only insofar as spotlighting those CPRs which would be more conveniently deployable without sacrificing significant clinical utility.

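### The test tradeoff is meant to show whether interaction rules earn their complexity, but its comparator is chosen by rank and need not be the same model's score without the rules

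*Protocol article*

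**What the plan says.** Section 2.12.1 (Overview) of the protocol article says the team will "construct two CPRs per model: one based on SHAP main effects and another incorporating both SHAP main and interaction effects", and the Models section says "LR, XGBoost, and MLP classifier models will be used to establish the updated CPR". That gives three non-augmented and three augmented CPRs. The CPR Development section says "Each of the CPRs will subsequently be augmented by integrating interaction effects", so each augmented CPR has exactly one counterpart that shares its base points and lacks only the rules.

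The CPRs are then pooled and ranked by net benefit. Table 3 (Interpretation column) states that, among those found useful, "we will rank the CPRs (including CHA_2_DS_2_-VASc) based on NB across the 0.01–0.20 risk thresholds".

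The CPR Evaluation section sets the trigger, "If an augmented CPR ranks among the three highest", and the comparator: "we will perform test tradeoff analysis to compare it with the closest-ranking non-augmented CPR". It describes the cost being traded as the inconvenience of scores that are "more unwieldy than their non-augmented counterparts".

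Table 3 (Analysis Plan column) gives the aim: the test tradeoff is to evaluate "whether any incremental benefit in clinical utility observed with augmented CPRs justifies the added complexity of incorporating accompanying rules". Both Table 3 (Interpretation column) and the end of CPR Evaluation also state a second, limited aim: to point out which CPRs could be used conveniently at little loss of clinical utility, without ruling out the more cumbersome ones. For MLP-derived CPRs, CPR Evaluation adds a question about whether a less interpretable model is worth its extra NB.

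**The concern.** The question about the rules is a within-model question: what does NB gain when interaction rules are added to a fixed set of base points? The comparator is instead picked from the results, by rank, with no requirement that it come from the same model. If it comes from another model, the NB difference contains the gap between two base scores as well as the effect of the rules, and the two cannot be separated.

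Selection by nearest rank also tends to pick a comparator with similar NB. CPR Evaluation reads small NB differences as a large tradeoff that may favour the simpler score, so the selection rule itself leans towards that reading, whatever the rules contribute. At stake is how the reported tradeoff is interpreted as evidence on the rules.

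**Working it through.** The plan gives no figure for this point, so there is none to reproduce. The check compares the stated aim with the comparator rule, then illustrates the size of the effect. All NB values and correlations below are assumptions.

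**1. Aim against rule.** The aim in Table 3 needs NB(X*) − NB(X), where X* is model X's augmented CPR. The rule gives NB(X*) − NB(Y), where Y is the non-augmented CPR nearest in rank. This splits as

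NB(X*) − NB(Y) = [NB(X*) − NB(X)] + [NB(X) − NB(Y)].

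The second bracket is zero by construction only when Y = X. Nothing else in the article restricts Y to X.

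**2. Effect on the tradeoff.** Take the tradeoff as 1/ΔNB, which fits the plan's statement that small NB differences give a large tradeoff. Assume XGBoost* 0.060, XGBoost 0.050 and LR 0.059, with the MLP base CPR below 0.059 (and CHA2DS2-VASc too, if eligible).
- Same-model pair: 1/(0.060 − 0.050) = 100.
- Closest-ranking pair, as written: 1/(0.060 − 0.059) = 1000.

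The reported tradeoff is ten times larger although the rules' contribution is the same.

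**3. Ties and direction.** Assume LR 0.062, LR* 0.060 and XGBoost 0.0595, with the other CPRs below 0.0595. LR is one place above LR* and XGBoost one place below, so they are equally close, and the plan gives no tie rule. If XGBoost is taken, the tradeoff is 1/(0.060 − 0.0595) = 2000 and positive. Against its own base the difference is 0.060 − 0.062 = −0.002: the rules reduced NB.

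**4. How often the comparator is not the own base.** Each CPR's NB was simulated as a model effect with variance ρ plus an independent part with variance 1 − ρ, for three models with two CPRs each, optionally with CHA2DS2-VASc as a seventh, independent entry. There were 20,000 runs per setting. For each augmented CPR in the top three, the nearest-ranked non-augmented CPR was found, with ties broken at random.

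| ρ | Six CPRs: not own base | Six: own base not even tied | Seven: not own base | Seven: own base not even tied |
|---|---|---|---|---|
| 0 | 66% | 58% | 75% | 68% |
| 0.5 | 55% | 46% | 64% | 54% |
| 0.8 | 43% | 32% | 51% | 39% |
| 0.95 | 31% | 18% | 39% | 22% |
| 0.99 | 24% | 8% | 31% | 11% |

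At ρ = 0 the first and third columns should be 2/3 and 3/4 by symmetry, which they match. Rank ties occurred in about 24–42% of cases across all settings.

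**5. Scale in patients.** A second simulation used 400 cohorts per event rate (5, 10 and 25%) and 691 test patients. The three models were LR and two bootstrap-perturbed versions, and ties went to the smaller NB difference. Tradeoffs from the median absolute difference were 6027, 3034 and 4195 for the closest-ranking comparator and 3285, 2013 and 3032 for the own base. Dividing 691 by each gives 0.11, 0.23 and 0.16 against 0.21, 0.34 and 0.23 of one true positive. The tie rule pushes towards small differences and the models are stand-ins, so these figures are used only for scale.

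**The case against.** The strongest reply is that the plan also states a deployability aim and limits interpretation to it. For that aim, the relevant alternative is any simpler score a clinician could use. Non-augmented CPRs from every model are point tables on the same features, so the source model makes no difference at the bedside. In step 2, the same-model figure of 100 makes the rules look worthwhile, while the closest-ranking figure of 1000 shows that a plain LR score does almost as well. This stands: the closest-ranking comparison answers a legitimate question and should not be removed.

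It also stands that the metric is descriptive, that all decision curves appear in one figure so same-model differences can be seen, and that in step 5 the tradeoff is large under either comparator. For MLP-derived CPRs a between-model comparison is partly intended.

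A reader might infer that the test tradeoff never measures the rules, that the plan makes a biased decision against them, or that CHA2DS2-VASc will regularly serve as comparator. The documents support none of these. The own base is sometimes the nearest CPR. No CPR is dismissed on this result. CHA2DS2-VASc is included in Table 3's ranking, but CPR Development uses the term non-augmented for the newly built scores.

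What the reply does not remove is the question about the rules written into Table 3. The closest-ranking comparison answers it only when the nearest CPR happens to be the model's own base.

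**Conclusion.** The point holds in a limited form. Table 3 asks whether the rules justify their complexity, and the comparator fixed in CPR Evaluation isolates the rules only when it is the model's own base CPR. Otherwise the NB difference mixes base model and rules, and choice by nearest rank tends to make it small.

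The mismatch follows from the text and needs no simulation. Its frequency does: 24–66% with six CPRs and random tie-breaking, or 8–58% on the stricter count, falling as the two CPRs of a model become more alike in NB. The documents give no NB values, so a claim that it happens often cannot be made from them. The consequence is confined to how a descriptive secondary measure is interpreted.

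**What to change.** In CPR Evaluation, for each augmented CPR in the top three, report the test tradeoff against the non-augmented CPR derived from the same model, and name this as the answer to Table 3's question on the rules. Keep the comparison with the closest-ranking non-augmented CPR as a separate deployability comparison.

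For MLP-derived CPRs, state that the interpretability question is answered by between-model comparison with the LR- and XGBoost-derived CPRs of the same form (both augmented or both not). Table 4 already plans to compare MLP-derived CPRs with both.

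The cost is a change of wording and a few more reported contrasts, all from NB values that the plan already computes.

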##### External Validation

The performance of CPRs often markedly declines when applied to independent datasets [125]. Regular, robust external validations are therefore indispensable to accurately assess a CPR’s generalisability over time and space. While some journals require an external validation section in CPR studies, the legitimacy of this requirement has been called into question [77]. Mandating a single ‘snapshot’ validation may inadvertently lead to selective reporting of favourable results from a specific setting, rather than promoting a thorough evaluation across diverse populations. This may prove particularly counterproductive when ML and DL models are involved, as these models can harbour embedded biases.

Given these considerations, we argue that the external validation of our CPRs deserves its own dedicated study, complete with a preregistered protocol that includes tailored power analyses and strategies to quantify patient heterogeneity. We hereby commit to a follow-up study that will not only strengthen the credibility of our CPRs but also contribute to advancing best practices in CPR research. External validation is not merely an item on a checklist, but a rigorous investigation in its own right, requiring careful planning and registration before execution.

##### Fairness

To enhance the fairness of our CPRs, we will explore how porous they are to any entrenched gender and age biases.

##### Gender Bias

There are concerns that CHA_2_DS_2_-VASc may overestimate stroke risk in women, particularly younger women and those who have no other risk factors [126]. We will supplementarily report discrimination, calibration, and DCA separately for male and female patients in order to determine whether the gender adjustment of our CPRs is warranted.

##### Age Bias

By treating age as a categorical and not a continuous variable, our CPRs may oversimplify the relationship between ageing, comorbidities, and AIS risk. After all, AIS risk does not abruptly rise on a patient’s 65th or 75th birthday. We will supplementarily report discrimination, calibration, and DCA separately for <65-, 65–74-, and ≥75-year-old patients to determine whether the age adjustments of our CPRs are warranted. DCA will also be performed for patients within the highest and lowest age deciles so as to compare the CPRs against the default strategies and identify any potential under- or over-treatment. This will be performed across all patients and as well as separately for male and female patients. Age-stratified analyses will be conducted across all patients as well as sub-stratified by gender.

##### Comment on Ethnic and Socioeconomic Biases

CHA_2_DS_2_-VASc was predominantly developed and validated using data from white European populations. It is encouraging that VISTA’s contributing trials included centres from diverse parts of Europe, North America, South America, Asia, and Oceania. However, we take notice of the limited representation of African populations, as only South Africa was included from the African continent. The underrepresentation of African populations is a serious obstacle to the global applicability of CPRs, and TRIPOD-P explicitly calls for the contribution of individuals with CPR expertise from Africa, as well as Asia, Central America, and South America [70].

VISTA did not record patient race and socioeconomic status (SES), meaning we will not be able to perform race- and SES-stratified analyses, nor report on the proportion of African American and Latino American patients, for example. It has been found that both African American and Latino American patients with CHA_2_DS_2_-VASc scores of two or more were less likely to receive NOACs than white patients [127]. While the disparity between Latino American and white patients did not persist after adjusting for SES, the difference between black and white patients remained significant. This highlights the critical need for population-based research cohorts for fine-tuning CPRs to existing health disparities [128].

